Insomnia Severity Index		●		●		●		●		●	●
Patient Health Questionnaire 15		●				●				●	●
Patient Health Questionnaire 9		●		●		●		●		●	●
Generalized Anxiety Disorder 7		●		●		●		●		●	●
Weight (in kilograms)	●	●				●				●	●
Adverse Events Log		●	●	●	●	●	●	●	●	●	●
Electrocardiogram	●			●		●					
TSQM-side-effects item			●	●	●	●	●	●	●	●	●
Proportion completing dose escalation phase						●					
Secondary Outcomes											
Substance Use TLFB-MA (Days Used)	●	●	●	●	●	●	●	●	●	●	●
Urine Drug Screen (positive MA)	●^d^	●	●	●	●	●	●	●	●	●	●
Substance Use TLFB-MA (Days Used)		●	●	●	●	●	●	●	●	●	●
Urine Drug Screen^c^	●^d^	●	●	●	●	●	●	●	●	●	●
TSQM-effectiveness item		●	●	●	●	●	●	●	●	●	●
Visual Analogue Scale for MA craving		●^t^	●^t^	●^t^	●^t^	●^t^	●	●	●	●	●
Amphetamine Withdrawal Questionnaire		●^t^	●^t^	●^t^	●^t^	●^t^	●	●	●	●	●
Severity of Dependence Scale		●								●	●
Adapted Opiate Treatment Index (HIV & crime scales)		●				●					●
TSQM-convenience & global satisfaction items		●	●	●	●	●	●	●	●	●	●
Proportion discontinuing once enrolled			●	●	●	●	●	●	●	●	
Price would Pay		●^b^	●^b^	●^b^	●^b^	●^b^					
Similarity to MA Visual Analogue Scale		●^b^	●^b^	●^b^	●^b^	●^b^					
Drug Effects Questionnaire 5		●^b^	●^b^	●^b^	●^b^	●^b^					
Acute Subjective Response to Substances		●^b^	●^b^	●^b^	●^b^	●^b^					
Trail-making Test		●^t^	●^t^	●^t^	●^t^	●^t^					●
Rey Auditory Verbal Learning Task		●^t^	●^t^	●^t^	●^t^	●^t^					●
Digit-span sequencing		●^t^	●^t^	●^t^	●^t^	●^t^					●
Flankers Test with no-go		●		●		●					●
Digit Symbol Substitution		●		●		●					●
Rapid Information Processing		●		●		●					●

*Abbreviations*: ^*t*^timed trough/peak measurements prior to study drug administration/4 h post, *TSQM* Treatment Satisfaction Questionnaire for Medications, *MOCA* Montreal Cognitive Assessment, *AUDIT* Alcohol Use Disorder Identification Test, *WTAR* Wechsler Test of Adult Reading, *MA* methamphetamine, *TLFB* Time-Line Follow Back questionnaire

^a^vital signs measured daily

^b^Measurement taken 4 h post study drug administration

^c^Urine drug screen for benzodiazepines, cannabis, cocaine, methadone, morphine/heroin and oxycodone

^d^Two urines positive for methamphetamine required for eligibility

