## Methods

### Design

The study is a phase 2, single group, outpatient study with a study period of 14 weeks, inclusive of screening and follow up. Screening will occur over 2 weeks (weeks −2 and −1), and eligible participants commenced on the escalation/de-escalation phase (week 1). Escalation of LDX will occur over 4 weeks, beginning at 100 mg/day, with weekly increases of 50 mg to a maximum 250 mg/day. After 2 weeks at 250 mg/day LDX, the dose of LDX will be reduced weekly by 50 mg/day, ceasing after 1 week at 100 mg/day. A follow up study visit will occur in week 12, 4 weeks after cessation of study drug. The study aims to enrol a sample of twenty participants who are seeking treatment for methamphetamine dependence. A diagrammatic overview of the study is given in Fig. 1. The protocol has been designed in accordance with CONSORT SPIRIT guidelines [27].

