### Safety and discontinuation

Specific adverse events resulting in participant discontinuation are: pregnancy checked through monthly urinary hCG tests where applicable; clinically significant hypertension (two consecutive readings of systolic blood pressure >160 mmHg or diastolic blood pressure >100 mmHg within an hour); persistent tachycardia (>120 beats per minute for >60 min) or clinically significant psychotic symptoms (as assessed by the principal investigator). Additional unscheduled visits occur if there is any concern regarding possible toxicity. Further reasons for participant withdrawal are the observed diversion of study drug, withdrawal of consent, missing three or more doses in a 7 day period or missing more than one extended data collection visit. An independent data safety and monitoring board has been established to ensure adequate safety outcomes and management of the study drug for the continuation of the study. It will first meet after 5 participants have commenced the study drug and completed up to the end of the dose escalation period (or discontinued prior) and then twice yearly. Any adverse effects experienced by participants will be treated by the study team, or referred to a specialist as required.

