#### Statistical analysis

Given the exploratory nature of the study, twenty participants will provide sufficient proof of the safety of the dose. While not powered to detect statistically significant effect sizes, findings will inform a planned randomised control trial of LDX for the treatment of methamphetamine dependence.

Descriptive statistics of proportion commenced on study drug who complete the study; proportion who achieve each dose; proportion who experience adverse event by type, severity and dose. Tolerability of LDX will be described using medians and interquartile ranges of TSQM side-effects scores. Continuous and categorical primary outcomes will be examined within a generalised linear mixed model framework [55]. Secondary outcomes measures changes in MA use, other substance use, craving, withdrawal, severity of dependence, risk behaviour scores and neurocognition will be tested for statistical significance using Wilcoxon rank-sum test for non-parametric data. The estimation of magnitude of effects of LDX on MA use will be calculated separately for those individuals that have and have not been adherent to counselling during the course of the study. Dose adequacy, medication acceptability, and potential for non-prescription use will be described using median scores and interquartile ranges at each dose. Analysis of urine drug results will follow established practice so that missing urine results are assigned as being positive for methamphetamine and the proportion of urines positive for methamphetamine will be reported. Missing data will be imputed using multiple imputation procedures.

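### Scoring every missing urine as positive, with no exception for mandated discontinuation, inflates urine positivity in a single-arm trial and mixes dropout with dose and time

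*Protocol article*

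**What the plan says.** The Statistical analysis section of the protocol article sets the urine rule: "missing urine results are assigned as being positive for methamphetamine and the proportion of urines positive for methamphetamine will be reported". The only reason offered is convention: "Analysis of urine drug results will follow established practice". No exception is made for the reason a urine is missing. The section also plans a significance test for change in methamphetamine use, but does not say that it uses urines. The sentence right after the urine rule reads "Missing data will be imputed using multiple imputation procedures" and does not say whether urines are included.

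The Safety and discontinuation section lists events that end participation. It begins "Specific adverse events resulting in participant discontinuation are: pregnancy checked through monthly urinary hCG tests where applicable; clinically significant hypertension" and goes on to "persistent tachycardia (>120 beats per minute for >60 min) or clinically significant psychotic symptoms (as assessed by the principal investigator". Other grounds are observed diversion and "withdrawal of consent, missing three or more doses in a 7 day period or missing more than one extended data collection visit".

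The Design section describes a single group with a dose order fixed by week, and "The study aims to enrol a sample of twenty participants who are seeking treatment for methamphetamine dependence". Table 1 schedules a urine screen in each of weeks 1 to 8 and in week 12, and its footnote d states "Two urines positive for methamphetamine required for eligibility".

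**The concern.** The rule treats a urine that was never collected because the protocol stopped the participant in the same way as one that a participant still on study failed to give. A participant stopped for pregnancy or a cardiovascular sign then enters the urine figure as a methamphetamine user at every later visit. The figure mixes two things: use, and absence from the study.

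In a trial with a concurrent control, the same rule would apply to both arms. Here there is no control, and the Discussion names that as a limitation. Because every participant goes through the doses in the same weekly order, accumulating withdrawals are also mixed with dose and calendar time.

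Change in methamphetamine use is the first secondary outcome listed, urine is its only objective measure, and the findings are meant to inform a planned randomised trial. A reduction could be understated there.

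**Working it through.** The article gives no dropout rate and no expected positivity, so there is no stated figure to reproduce. The check shows what the rule does over an assumed range.

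**Inputs from the article**
- N = 20, one group (Design).
- 250 mg in weeks 4 and 5, then reduction in weeks 6 to 8 (Design). In the text at hand the dose row of Table 1 sits one column earlier. That may be a fault of extraction, so the Design section is used.
- Nine post-baseline urines per participant: weeks 1 to 8 and week 12 (Table 1).
- Baseline positivity 100% by eligibility (Table 1, footnote d).

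**Assumptions**
- 2, 4 or 6 of 20 withdrawn by week 8, so d = 0.1, 0.2 or 0.3.
- True positivity p = 0.4, 0.6 or 0.8, the same in withdrawn and retained participants.
- No urine after withdrawal, and all scheduled urines in the denominator.

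**Step 1: a single record.** A participant withdrawn after week k with only negative urines scores (9 − k)/9 positive.
- k = 2: 7/9 = 78%, against 0/2 observed.
- k = 4: 5/9 = 56%, against 0/4 observed.

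These are extreme cases. They show the mechanism, not its likely size.

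**Step 2: the cohort in a given week.** Reported positivity is r = d + (1 − d)p, so the inflation is r − p = d(1 − p). At week 8, in percentage points:

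| Withdrawn | p = 0.4 | p = 0.6 | p = 0.8 |
|---|---|---|---|
| 2/20 | 6 | 4 | 2 |
| 4/20 | 12 | 8 | 4 |
| 6/20 | 18 | 12 | 6 |

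The range is 0.1 × 0.2 = 2 points to 0.3 × 0.6 = 18 points.

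**Step 3: if withdrawn participants differ.** Let w be true positivity among the withdrawn. The inflation over the cohort's true value is then d(1 − w). It equals the table when w = p and is zero when w = 1.

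**Step 4: effect on change from baseline.** Suppose true positivity falls from 100% at entry to 45% at week 8, with 4/20 withdrawn. Reported week-8 positivity is 0.2 + 0.8 × 0.45 = 56%. A true fall of 55 points is reported as 44.

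**Step 5: pattern over the taper.** If withdrawals are spread evenly over weeks 1 to 8, then d at week 5 is 5/8 of d at week 8. With p constant, the artefact from the last 250 mg week (week 5) to week 8 is (3/8) × d × (1 − p):
- smallest: 0.375 × 0.1 × 0.2 = 0.75 points;
- largest: 0.375 × 0.3 × 0.6 = 6.75 points.

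One participant in 20 is 5 points.

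**Step 6: must positivity rise in the taper?** No.
- If all four withdrawals fall by week 4 and p = 0.6, the reported value is 0.2 + 0.8 × 0.6 = 68% in each of weeks 5 to 8, which is flat.
- If true positivity falls from 90% at week 1 to 45% at week 8, the reported series still falls, to 50.5%, 56% or 61.5% with 2, 4 or 6 withdrawn.
- If d goes from 0.1 at week 5 to 0.2 at week 8 and p is 0.6 at week 5, reported week-5 positivity is 0.1 + 0.9 × 0.6 = 0.64. A fall in p to (0.64 − 0.2)/0.8 = 0.55 by week 8 cancels the artefact.

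**The case against.** Several points on the other side carry weight.

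- **The stops may themselves reflect use.** A reader might infer that all the discontinuation grounds are unrelated to methamphetamine. The article does not support that. Its Background lists psychosis and acute cardiovascular events among the harms of stimulant use, and abstinence is not required. Missed doses and visits are the cases that the convention is meant for. Of the listed grounds, only pregnancy is clearly unrelated. This stands, and by step 3 it can shrink the bias.
- **The taper.** A reader might infer that the rule produces an apparent return to use as the dose comes down. It does not follow. Only the imputed share from withdrawals is barred from falling; total positivity may be flat or falling (step 6). Toxicity related to dose would also be expected mostly before or at 250 mg, which leaves less artefact for weeks 6 to 8.
- **Toxicity and dropout are not hidden.** Completion, dose reached and adverse events are reported separately, and Table 1 schedules the proportion discontinuing in weeks 1 to 8. Given d for each week, a reader could recover p = (r − d)/(1 − d). That works only if the weekly shares are published and no urine is missed intermittently.
- **There is a second measure.** The Timeline Follow-back interview also records use and is not subject to the rule.
- **The literal reading may not be intended.** The article does not say whether discontinued participants still give urines or which denominator applies. The full protocol or analysis plan may settle both.
- **The bias is conservative.** From a baseline of 100% it cannot create a false benefit.

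These points limit the finding but do not remove it. The article fixes the rule and names one urine figure, and nothing in it separates a mandated stop from a missed urine.

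**Conclusion.** The point holds in limited form. As written, the rule adds d(1 − p) to urine positivity, with no control arm to offset it. Under the assumed ranges this is 2 to 18 points at week 8. It rests on three assumptions that the article does not confirm: no urines after discontinuation, all scheduled urines in the denominator, and similar positivity in withdrawn and retained participants. If those who withdraw are all using, the inflation is zero.

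The bias pulls toward no reduction from baseline and cannot be told apart from dose and time. It does not by itself produce a rise during the taper. The damage is confined to one descriptive secondary outcome in an exploratory study, and the primary safety outcomes are untouched. The urine rule and the multiple-imputation sentence also need reconciling, since both as worded cover missing urines.

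**What to change.** In the Statistical analysis section:

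1. Keep the proportion with all missing urines set to positive, label it an upper bound, and state whether it covers urines due after discontinuation.
2. Beside it, for each week, report the proportion positive among urines collected, with the number collected and the number missing by reason: intermittent miss, safety or pregnancy discontinuation, other withdrawal.
3. Interpret a change over the ascending or descending doses only where both figures agree.
4. State that the multiple-imputation sentence does not apply to urines, or say how it does.

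The cost is one extra set of columns and a few sentences, with no new data. The collected-only figure should not replace the present one. It may be too favourable if those who drop out are using, which would trade a conservative bias for a survivor bias in favour of the drug. Neither figure should stand alone.

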## Discussion

Research related to pharmacotherapy options for the treatment of methamphetamine dependence has been often underpowered, with some concerns of under-dosing also noted [6]. The publication of study protocols such as this not only represents good clinical trial practice, but allows for the sharing of methodology in phase 2 studies in addiction pharmacotherapy research. Safety data for this population are essential to ensure dosing at optimal levels in larger scale trials. As abstinence from methamphetamine use for the period of the trial is not mandatory, the safety data elicited from this trial may be applied to more “real-world” scenarios, such as outpatient programs for stimulant users. Limitations of the study include the lack of a control group and the small sample size. While this is typical of numbers required for safety data, it limits the generalizability of the secondary efficacy measures. The trial is open-label, and non-randomised and thus participants may be subject to expectancy effects. To mitigate this, subjects and dispensing nurses are aware of the minimum and maximum doses, but blinded to the dose and to the escalation and de-escalation regimen. Though concurrent methamphetamine use is dependent on self-report, a validated tool (the TLFB interview) is used to obtain this data. Determining the safety and dose optimization of LDX within the target population will provide valuable data for phase 3 studies on the efficacy of LDX to treat methamphetamine dependence.

## Abbreviations

AUDIT: Alcohol use disorders identification test
CONSORT: Consolidated standards of reporting trials
ECG: Electrocardiogram
hCG: Human chorionic gonadotropin
LDX: Lisdexamfetamine
SPIRIT: Standard protocol items: recommendations for interventional trials
TEAE: Treatment emergent adverse events
TLFB: Time line follow back interview
TSQM: Treatment satisfaction questionnaire for medications
WTAR: Wechsler test of adult reading
